## Abstract

**Background:**

Transition from paediatric to adult heath care services is a challenging time for many adolescents with chronic illnesses and may include deterioration in illness control as a consequence of inadequate self-management skills, poor understanding of their chronic illness and failure to engage with adult services. Successful transfer of health care requires the development of self-management skills and increased autonomy. Mobile technology has been proposed as a modality to assist this process. Evidence is limited and generally restricted to illness specific applications. The TransitionMate app (TMApp) is a generic (non-illness specific) mobile application designed to support young people with chronic illness in their transition from paediatric to adult health care services. The overall aim of the study is to assess the effectiveness of TMApp in improving engagement and retention of adolescents with chronic illness within adult healthcare services, as well as preventing the deterioration in illness control and unplanned hospitalisations.

**Methods:**

The TransitionMate trial is a dual centre, pragmatic, single arm, mixed methods cohort study conducted within two university teaching tertiary paediatric hospitals in Australia. Data collection points are planned at 0, 6, 12 and 18 months. Outcome indicators include: usage of TransitionMate, engagement with adult services, quantitative markers of illness control, and unplanned hospital admissions. Data are collected through telephone interviews with the participants, their primary healthcare providers, electronic medical records and de-identified mobile application analytics. The development of the application involved co-design with recently transitioned young people with a number of chronic illnesses as well as online user experience in younger adolescents.

**Discussion:**

The TransitionMate study is the first identified trial of a generic mobile application designed to support adolescents with chronic illnesses during the transition process. Results are expected to provide novel insights into the value of technological tools in the transition space, especially their effectiveness in improving both the transition process and clinical outcomes of adolescents with chronic illnesses. Furthermore, the approach of a pragmatic study design may help identify research methods better designed to overcome inherent challenges in research involving adolescents, transition of care and use of mobile application technology.

**Trial registration:**

Registered retrospectively as of 30/1/2020 with Australian New Zealand Clinical Trials Registry: ACTRN12620000074998.

**Supplementary Information:**

The online version contains supplementary material available at 10.1186/s12913-022-08536-8.

## Value of a pragmatic trial in studies involving

Transition of care in chronic illnessAdolescentsEffectiveness of a mobile application designed to change behaviour

## Introduction

### Background and rationale

Chronic illnesses are long term conditions that if left untreated or incorrectly managed, may cause numerous complications that seriously affect overall long term health and wellbeing. To maintain optimal physical health, a young person with a chronic illness needs to perform repetitive and specific illness management tasks and often maintain a lifestyle with regimentation and restricted conditions. For young people with chronic childhood illnesses, expectations around self-management often change dramatically as they transition from paediatric to adult care [1, 2].

Transition refers to the planned movement of adolescents or young adults with chronic illness from paediatric centred care to adult health care systems [3]. This process requires the young person to develop increased autonomy and independence from parents/guardians. Young people also have to adjust to care from new clinicians in adult healthcare services, where the management approach is more individual with expectations of full autonomy, and less family-oriented [4, 5]. Additionally, during this transitional phase, the treatment itself may change or require modification, representing an additional challenge. During this unique life stage of emerging adulthood, young people also need to incorporate their illness management processes into other major transitions such as leaving school or home, entering employment or tertiary studies and entering new relationships [6–8]. It is during this time that there is often deterioration in illness control and even unplanned hospitalisations as a result of inadequate self-management and failure to respond to physical alerts of illness deterioration [9–11].

Another important factor to consider in chronic illness self-management of young people is the influence of psychological well-being, with Adam and colleagues in the United States in 2019 reporting the adjusted risk of incidental mental health conditions being 51% greater in youth with chronic physical conditions when compared with those without [12–15]. Therefore, with the complexity of the transition process and its role in shaping the future health and lives of these young people, it is imperative that the health care system continues to find new ways to motivate and support young people to improve their chronic illness self-management. The purpose of this study is to investigate how new digital technology can be used to support environments where young people are focused on attaining autonomy in many aspects of their lives.

Mobile technology is widely used by adolescents and young adults, creating a unique opportunity to explore innovative ways of communicating and supporting young people with their chronic illness self-management during the transition to adult health care systems [3, 12, 16]. To date, there is limited evidence regarding use of mobile phone applications aimed at supporting self-management in adolescents living with chronic illnesses, with the available ones generally being disease specific applications.

Majeed-Ariss and colleagues in 2015 conducted a systematic review to examine the literature (between 2003 to 2014) regarding the effectiveness of mobile apps designed to support adolescents in the management of their physical chronic conditions [17]. A key conclusion from the study was the significant lack of evidence-based apps in this field, highlighting the need for further investigations and research. A meta-analysis drawing on data published between 2006 and 2016 examined the use of mobile health interventions in improving health outcomes in young people [18]. The study showed that digital technology can be effective in eliciting meaningful improvements in paediatric health behaviour and associated health outcomes. However, the average age of participants was 11.4 years, and many of the papers focused on interventions targeting care givers, or on immunisation adherence, thereby limiting conclusions around adolescents’ self-management with chronic illnesses.

A recent systematic review conducted by Virella Pérez and colleagues examined the literature published from 2013 to 2018 on the utility and effectiveness of mobile and/or web-based health applications that support self-management and transition in young people with chronic physical illnesses and identified that apps were invariably illness specific [19]. The lack of literature and clinical data remains a key theme and the review was unable to provide evidence for effectiveness of this approach. However, the review did provide insights into future study design with reference to the development, evaluation and effectiveness of applications tailored for adolescents with chronic illnesses, including the involvement of adolescents in such designs [19, 20]

Traditional models of healthcare, based on face-to-face meetings and information exchanged directly between the patient and the healthcare professional, are no longer the only communication avenue and approach. The ubiquitous nature of mobile devices offers an opportunity to explore new means of interacting with young people over the management of their chronic condition in the period between when they leave paediatric health care and finally engage with adult healthcare. For example, mobile phones and applications can be used for data management, and a reminder system for self-management tasks and appointments. Applications could also serve as a reporting tool for information such as a patient’s emotional well-being over time, as well as real time data on events, problems, thoughts or feelings almost anywhere, anytime. Much of this information can be remotely extracted as the digital footprint [21, 22]. This digital footprint, when applied appropriately, may be a valuable tool in understanding and improving the healthcare experience of patients, including during the transition process.

Despite the potential benefits of mobile applications, there is a significant void in generic evidence based mobile tools to support adolescents with chronic illnesses in transitioning from paediatric to adult healthcare. Furthermore, despite the intuitive assumption that young people would readily use these media in their healthcare management, there is a lack of rigorous evaluation and empiric research data to provide evidence-based support for this assumption. The conclusions from literature reviews, along with the growing need for innovative and effective tools to support the transition process for young people, have led our investigators to create a purpose-built mobile application called TransitionMate. This mobile application was designed to be a generic tool to support young people with a chronic illness during their transition from the paediatric to adult healthcare system. The application aimed to provide some support at a time when young people may be resisting assistance from family as a mark of independence, and particularly between the last paediatric and first adult health are visits.

The lengthy development of, and technical challenges of the TMApp, together with analytics, will be submitted as a separate manuscript. The application we describe in this manuscript is the final product for clinical trialing.

Our study aims to evaluate the effectiveness of a mobile health intervention (TMApp) in supporting self-management and transition to adult healthcare services for young people with chronic illnesses.

### Objectives

#### Primary objective

To examine the effectiveness of the TMApp on rates of engagement with adult services in young people with chronic illness (such as type 1 diabetes mellitus, inflammatory bowel disease, cystic fibrosis, mixed connective tissue disorders) transitioning from paediatric to adult care.

#### Secondary objectives

To examine the rates of retention with adult services at 12 and 18 months in young people with a chronic illness who have successfully transitioned (i.e. successfully engaged) to adult services.To understand how disease control changes during the first 18 months post transitionTo understand if the use of the TMApp can assist with preventing deterioration of chronic illness control in young people in the 12 months post transition.

### Trial design

The trial is designed to be a two centre, pragmatic, single arm, mixed methods cohort study. As this is a single arm study, there will be no randomisation or allocation process on recruitment. Results will be compared with existing historical data from our previous research as well as others.

Source of historical data from the following source:Perry L, Steinbeck KS, Dunbabin JS, Lowe JM. Lost in transition? Access to and uptake of adult health services and outcomes for young people with type 1 diabetes in regional New South Wales. Med J Aust 2010 Oct;193(8):444–9.Audit of 239 young adults aged 18–28 years with type 1 diabetes accessing five adult diabetes services before 30 June 2008 in three geographical regions of New South Wales [23]Garvey KC, Markowitz JT, Laffe LMB. Transition to Adult Care for Youth with Type 1 Diabetes. Curr Diab Rep 2012 Oct;12(5):533–541 [24].Data were collected between August 2004 and October 2005 through face-to-face interviews with over 200 clinicians in 68 clinical services in tertiary paediatric hospitals in New South Wales, providing information on approximately 4200 patients

### Explanation for the choice of comparators

Based on the number of patients which fits the eligibility criteria within the hospital network each year, and the anticipated recruitment based on previous adolescent studies of 1:4 approached actually consenting, it was unlikely that adequate power would be achieved if we were to recruit for a comparator group within the resourced time frame available. The necessary updates and debugging in mobile technology and their cost, coupled with the uncertainty of success based on previous literature guided the choice of a single arm study. It was important that we had more knowledge about the TMApp’s utility and durability of use before progressing to a comparator study.

## Methods: participants, interventions and outcomes

### Study setting

Participants will be recruited from the paediatric outpatient clinics of the two tertiary paediatric hospitals within the Sydney Children’s Hospital Network - Sydney Children’s Hospital at Randwick and The Children’s Hospital at Westmead - which are both located in Sydney, Australia.

Suitable patients aged 16 years and over with a chronic illness requiring transition to adult services and who are in their final year of paediatric care/attending their penultimate paediatric appointment will be identified by the treating team or clinic staff and will be approached for recruitment in the study by a member of the research team. Recruitment in the penultimate appointment is to reduce the risk of any paediatric intervention confounding the effect of the mobile application.

### Eligibility criteria

#### Inclusion criteria

Current patients of the Sydney Children’s Hospital Network who have a chronic physical illness (defined as a long term physical health condition that is likely to have consequences for the overall wellbeing of a patient if inappropriately managed or left untreated).16 years of age and overTransitioning to adult healthcare services within the next 12 monthsConsent to use the TransitionMate app and follow-up for 18 months

#### Exclusion criteria

Intellectual disability affecting use of mobile phone applicationPrimary diagnosis of mental health disorderNo access to personal smartphone

### Who will take informed consent?

Patients from subspecialty outpatient clinics at Sydney Children’s Hospital or The Children’s Hospital at Westmead who are considered appropriate by their clinical team will be approached and consented in person by a research investigator. Adolescents and their parent/guardians will be provided with an information sheet about the study. If the young person is 18 years of age they will be able to sign the consent form independently. If they are aged between 16 to 18 years of age, our institutional Human Ethics Research Committee (HREC) requires a parent/guardian signature for consent. Written consent (Additional file 1-Patient informed consent form) will be obtained from all participants.

### Interventions

#### Intervention description

##### Definitions

Application – TransitionMate mobile applicationEngagement – At least one attendance to the adult service in the preceding 6 months at the 6 months follow-up.Retention – At least one further attendance to the adult service in the preceding 6 months at 12 and 18 months follow-up.

##### Application development

The TMApp was initially designed through a collaboration between The School of Electrical and Information Engineering, The University of Sydney, Australia, The Academic Department of Adolescent Medicine at The Children’s Hospital at Westmead, Sydney, Australia and the Agency for Clinical Innovation, one of the pillars of New South Wales (NSW) Health, NSW, Australia. The app was designed to support self-management and transition from paediatric to adult care in young people with a chronic illness. It allows young people to develop self-management skills by: setting reminders for treatments required, medications or appointments. The six key features are: To do list; Contacts; Measures; Images; Medications; and Moods which are described below. These functions increases accessibility to important healthcare information for the young people as long as they have their mobile phones with them. Furthermore, they are able to email relevant information to care providers as required.

The TMApp requires the young person to input their own health related data, and we anticipate the initial set up of the app and input of health related data to take no more than 45 minutes. All health related data are stored locally on the patient’s device and do not get uploaded onto a server. Nor is it communicated with health care providers. The research team will be able to obtain a ‘digital’ footprint of all the participants’ interactions with the app. This will be de-identified group data which allow the research team to understand how frequently the app is used, which functions are most used, and how much time is spent on the app and each function. However, there is no ‘tracking’ of individual patient information in the sense that none of the information the young person has input into the app is relayed back to the app developer/health professionals or anybody else including the developers who provide the data. Patients are free to share their information with relevant health professionals if they so choose.

##### Intervention: downloading and use of the TransitionMate mobile phone application to assist transition of adolescent from paediatric to adult clinic services

The TransitionMate mobile phone application will be downloaded onto the participant’s mobile phone once the study has been explained and consent has been obtained. Download is performed by the participant under the guidance of the researcher. The download will be available from the Apple Store (ios) or Google Play Store (android). Use of the application would involve the participant independently opening the mobile application and using the features within. These features are:

*To do list*

*Measures of illness control*

*Contact list*

*Medication Lists*
*Images* (Take and save photos)
*Mood tracker using words or emojis*

The number of times the intervention (TMApp) and the features are used is determined by each participant. TMApp usage will be reviewed at the 6, 12 and 18 months by follow up phone calls (Additional files 4, 5, 6). These self-report data can be broadly compared to the application data analytics, which are cohort only data. Up to 5 attempts will be made to contact each participant via a telephone call at each of the 6, 12 and 18 months’ time points. A SMS message will be sent if the call is not picked up with contact details provided for a return call when it is convenient for the participant. Participants will no longer be contacted should they express at any time that they would not like any further communication with regards to the study.

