### Other data collection

The following data will be collected at baseline: gender, date of birth, ethnicity, diagnosis, young person’s email and mobile phone number, and one parent’s contact number and email (Additional file 8). We will record the standard transition care which the young person has received. Established transition services in our patient population includes ACI Transition Care Service, Trapeze Transition Service [25, 26] and joint paediatric and adult clinics. The NSW Health Agency for Clinical Innovation (ACI) Transition Care Service is a state-wide care coordination service responsible for supporting young people (aged between 14 and 25 years) with chronic illness/disability as they move from children’s health services to adult health services. Trapeze is part of the Transition Care Network and provides a supported transition into adult care for patients aged 14–25 within the Sydney Children Hospital Network. We will also obtain the details of the adult service that the treating paediatric team has referred the young person to. Included in the consent is collection of EMR data on measures of illness control and frequency of visits to the paediatric service in the previous 12 months.

Table 1 shows a sample list of conditions and relevant illness markers compiled in consultation with on the Clinical Services which have agreed to take part in the study. If other conditions not mentioned here are included, the research team will determine the preferred control marker in consultation with the respective clinical team.

**Table 1 Tab1:** Sample list of illness markers for chronic illnesses

Chronic illness	Illness marker
Acquired brain injury	Functional Independence Measure (FIM), the Glasgow Outcome Scale (GOS), and the Disability Rating Scale (DRS)
Autoimmune thyroid disease	Free T4; Free T3; TSH
Congenital Adrenal Hyperplasia	17 OHP; Plasma Renin Ratio; Testosterone, Androstenedione, Dehydroepiandrosterone sulfate (DHEAS)
Cystic fibrosis	FEV_1_; Weight
Duchenne muscular dystrophy	Creatinine kinase; Lung function test; GMFCS
Epilepsy	Number and frequency of seizures
Inflammatory bowel disease - Crohn’s, Ulcerative colitis	Weight; CRP; Faecal Calprotectin; ESR
Diabetes (Type 1 and 2)	HbA1c
Chronic liver disease, including Glycogen storage disorders and Transplant	Liver function tests and albumin level
Phenylketonuria	Serum Phe and tyrosine levels
Systemic lupus erythematosus	Antinuclear antibodies

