#### Engagement and retention with adult service

Successful engagement with the adult service at 6 months will be defined as confirmed attendance at least one appointment with the adult service by six months post discharge from paediatric care (i.e. after the last paediatric appointment). This will be considered as a *successful transfer* to adult services. This number is chosen because most chronic conditions have guidelines on the optimal number of specialist visits per year with a frequency varying from 3 to 6 months. Routine annual visits are less likely and will be recorded as such.

*Engagement* with the adult service will be assessed, with consent of the young person/parent, (provided at enrolment) via phone call to the young person and nominated adult service at 6 months post discharge from paediatric care. If the young person has not attended the service they were referred to, they will be asked if they are attending an alternate service and for consent to contact this service. Young people who cannot be contacted at 6 and 12 months post discharge from the paediatric service will be considered to have unsuccessful engagement and be a *failed transfer* to adult care.

*Retention* within the adult service will be defined as at least one confirmed attendance with the adult service in the preceding 6 months at 12 and 18 months follow up. These data will be collected, with consent, via phone call to the young person and the adult service to obtain information regarding attendance at the adult service at 12 and 18 months follow up. Young people who cannot be followed up at 12 and 18 months post discharge from the paediatric service will be considered to not be retained by the adult service (*failed retention*).

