## Discussion

This is likely to be the first trial of an application which has been developed as a generic tool to support transition from paediatric to adult health care. There is a paucity of literature considering the final active phase of transition. This is not surprising as this study is challenging given that the participants are moving to multiple care centres, young people change phones, the engagement in the study is likely to be a low priority and our functional application is competing with any number of attractive and engaging commercial applications which have the capacity to be rapidly modified by user feedback. The recruitment of adolescents to research studies has historically been challenging [27, 28]. This is particularly so with the transition phase as we are aiming to recruit these young people in their final year of paediatric care before they transition from paediatric to adult services. The diversity of the respective transition processes and challenges faced by the young people with chronic illnesses may also impede on our recruitment. Therefore, significant emphasis has been made by the researchers to inform, collaborate and maintain communication with the different clinical teams throughout the recruitment process. The identification of a contact person for each clinical team is an important step in this. Every effort will be made by the researchers to accommodate to the young people and clinical teams in order to minimise interference to their clinical care. No additional appointments are required for the recruitment process as the researchers will travel to meet the potential recruits at their planned clinics or admission as part of their routine medical care.

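### Participant follow-up is described as calls and an SMS only, although an email and parent details are held, and the contact-based failure rule can turn avoidable non-contact into failed transfer

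*Protocol article*

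**What the plan says.** All references are to the protocol article.

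- **Reaching the participant.** The section on downloading and using the app says "Up to 5 attempts will be made to contact each participant via a telephone call" at each of 6, 12 and 18 months, and "A SMS message will be sent if the call is not picked up with contact details provided for a return call". Contact stops if the participant asks for that. The Participant timeline likewise lists a call or text to the young person and no other route.
- **Contact details held.** Other data collection records "young person’s email and mobile phone number, and one parent’s contact number and email". No section gives the email or the parent's details a use in follow-up.
- **Foreseen problem.** The Discussion notes that "young people change phones".
- **Scoring.** Engagement and retention with adult service states: "Young people who cannot be contacted at 6 and 12 months post discharge from the paediatric service will be considered to have unsuccessful engagement", which it labels a failed transfer. The same section scores those who cannot be followed up at 12 and 18 months as failed retention. The missing-data section treats data that stay missing as non-engagement.
- **Other outcome sources.** Engagement is assessed "via phone call to the young person and nominated adult service at 6 months post discharge from paediatric care", with consent taken at enrolment. The Participant timeline allows a written request to the adult service. Primary outcome accepts either the adult service or self-report, supplemented by hospital databases.
- **App use.** Individual app use is self-reported at the follow-up calls and covered again in the 12-month interview. The analytics are available for the cohort only.

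**The concern.** The call and the SMS go to the same phone, so a changed number defeats both. The protocol expects this to happen and holds two further routes, but its stated contact sequence uses neither. The effort spent on tracing then feeds into the endpoint, because the scoring rule is worded on contact with the young person.

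Three kinds of information are exposed:

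1. **Attendance at an alternate service.** The protocol learns of such a service, and obtains consent to contact it, by asking the young person. A call to the nominated service will not reveal it, and a hospital database may or may not.
2. **Attendance that the nominated service confirms for someone not reached.** Primary outcome would count it. The contact-based rule, read literally, would fail it. No section says which prevails.
3. **Individual app use.** Statistical methods lists app use as a predictor of outcomes, and a secondary outcome relates it to illness control. No adult-service record can replace it.

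The first two lower the engagement percentage for reasons unrelated to engagement. The third loses data on the exposure of interest.

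**Working it through.** **1. Reproduce the plan's figure.** Sample size gives 49 evaluable participants, 30% attrition, one-sided 5% alpha, at least 80% power and a reference rate of 70%.

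- Inflation: 49 / (1 − 0.30) = 70, as stated.
- Statistical methods requires the lower limit of the exact 90% interval to exceed 70%. That limit is the 5th percentile of Beta(x, n − x + 1). At n = 49 the smallest qualifying count is 40 (81.6%, lower limit 70.1%), with exact type I error 0.048.
- The alternative is not stated. Power is 0.749 at a true rate of 84% and 0.809 at 85%, so about 85% is the smallest rate consistent with the claim. I use 85% as an assumption, with 90% alongside.

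**2. The rule when non-contact counts as failure.** People scored as failures stay in the denominator, so I take all 70 as analysed (assumption). The smallest qualifying count is 56 of 70 (80.0%, lower limit 70.5%, type I error 0.041). One wrongly failed participant costs 1/70 = 1.4 percentage points.

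**3. Effect of unrescued non-contact.** Let p be true engagement and c the share neither reached nor credited through the adult service or databases. If c is independent of engagement, the scored rate is p(1 − c), and the chance of meeting the rule is P(X ≥ 56) with X ~ Binomial(70, p(1 − c)).

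| c | scored rate, p = 85% | chance | scored rate, p = 90% | chance |
|---|---|---|---|---|
| 0% | 85.0% | 0.906 | 90.0% | 0.997 |
| 5% | 80.75% | 0.633 | 85.5% | 0.925 |
| 10% | 76.5% | 0.298 | 81.0% | 0.653 |
| 15% | 72.25% | 0.091 | 76.5% | 0.298 |
| 20% | 68.0% | 0.018 | 72.0% | 0.084 |

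Independence is the unfavourable case. At c = 10%, 7 people are involved. Failing them removes 7 × 0.85 = 5.95 expected successes if they engage like the rest, but 7 × 0.50 = 3.5 if only half of them engage (also assumed).

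**4. What survives when the phone fails.**

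| Information | Still obtainable without the participant? |
|---|---|
| Attendance at the nominated service | Yes, from the service or databases, but the contact-based rule may still score failure |
| Attendance at an alternate service | Only if a database shows it |
| Individual app use | No |

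**The case against.** The strongest reply is that attendance does not depend on reaching the participant. The nominated service is contacted as well, by phone or in writing, and hospital databases supplement it. The missing-data section imputes non-engagement only where data remain missing. This stands, and it is why c in the table means non-contact that no other source rescues.

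Second, the article is condensed and nowhere says that email or a parent will not be tried. A reader might infer that these routes are ruled out; the text does not support that. But this is not plain silence either: the number of attempts, the time points, the SMS fallback and a stopping condition are all written down, and the sequence as written ends at the phone.

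Third, the failure rule refers to non-contact at 6 and 12 months, so missed calls at one time point do not clearly trigger it. This also stands.

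Fourth, the bias is conservative: it lowers the engagement rate and so cannot by itself create a false claim of effectiveness. That is true, but it does not excuse a loss that details already on file could reduce, and it does nothing for the app-use data.

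Finally, asking a parent to step in could prompt attendance in a single-arm study of independent engagement, in an age group that the Introduction describes as resisting family help. This is a fair limit on the remedy and shapes it below.

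**Conclusion.** The point holds in a limited form. The described route to participants omits contact details that the study already holds, and the failure rule is worded on contact and not reconciled with the other accepted sources of attendance. The avoidable loss falls mainly on people at an alternate service, on people failed despite adult-service confirmation, and on individual app-use data.

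The size cannot be fixed from the document. With 85% true engagement, 70 analysed and non-contact independent of engagement (all assumptions), unrescued non-contact of 5%, 10% or 15% lowers the chance of meeting the rule from 91% to 63%, 30% or 9%.

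Two stronger readings are tempting. One is that a changed phone number by itself produces a primary-outcome failure. The document does not support this, given the adult-service and database checks and the wording of the non-contact rule. The other is that the planned 30% would all be scored as failures. In that case at most 49 of 70 (70.0%, lower limit 59.7%) could succeed, and the rule could not be met. But the 30% is predicted attrition, which may include people who withdrew, and it is not a non-contact rate.

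**What to change.** - **Contact sequence (section on downloading and using the app).** After the calls and SMS, send one email to the participant at 6, 12 and 18 months. Then, where the consent covers it and the participant has not asked for contact to stop, make one neutral request to the recorded parent for current contact details only, with no mention of clinic attendance.
- **Scoring (Engagement and retention with adult service).** Assign failed transfer or failed retention for non-contact only after the adult-service and hospital-database checks also show no attendance.
- **Reporting.** Give non-contact separately from confirmed non-attendance.

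The cost is a few minutes per unreached participant and a check that the consent wording covers the parent route, including once the participant is 18. No new data items are needed. A small risk remains that contact with a parent prompts attendance, which is why the request is limited to contact details.
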